## Assignment of interventions: allocation

### Sequence generation {16a}

Study participants will be assigned to a study arm via a randomly generated list on REDCap using the Clinical Research Database (CRDB) system at Memorial Sloan Kettering Cancer Center, which allows for off-site and off-hours randomization, as needed. Randomization will be stratified by language (English and Spanish) and recruitment site. The recruitment sites for this study are MSK, Lincoln Medical and Mental Health Center, and Montefiore Medical Center.

### Concealment mechanism {16b}

Study participants will be asked to complete their baseline survey prior to being informed of their study arm assignment.

### Implementation {16c}

Once the participant is consented to the study, the consenting professional will sequentially assign the participant to the intervention or the control arm identified in the randomization list, provided by the Department of Epidemiology and Biostatistics at MSK using a computer program to generate the list of randomization assignments in REDCap.

## Assignment of interventions: blinding

### Who will be blinded {17a}

Due to the nature of this study, it is not possible to blind participants or providers to the assigned treatment. Any tainting of our findings due to non-blinding would be anticipated to diminish our finding of a difference between treatment arms, however, rather than supporting a finding of a difference where there is none. All study procedures will be conducted to ensure complete transparency at the conclusion of the study, such that a Consolidated Standards of Reporting Trials (CONSORT) diagram may be constructed to describe recruitment and randomization in detail [49]. Moreover, the procedures followed, including the details of the interventions, will be described in rigorous detail and relevant materials (e.g., the app and information booklet) will be made available so that others may reproduce and extend our findings.

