### Outcomes {12}

The primary endpoint of the trial is self-reported employment status 4 months following the completion of treatment. This is the same primary endpoint as was used in the BCW study [7]; timing the assessment of employment status based on the end of treatment rather than the date of diagnosis provides an assessment that is comparable across participants, regardless of the timing between diagnosis and start of treatment. Depending on disease characteristics, provider recommendations, and patient preferences, participants will undergo different chemotherapy regimens with differences in cycle length and total number of cycles. They, therefore, will vary in their overall chemotherapy treatment period. Our endpoint of employment status 4 months following the completion of all treatment, consequently, has a shared interpretation across types of therapy. Two additional assessments will allow us to measure long-term employment status (1 and 2 years after completion of treatment). Patients working full-time or part-time will be considered to be working (job retained) regardless of whether they worked full-time or part-time at baseline.

Secondary study endpoints include change in self-efficacy to ask an employer for accommodations, receipt of workplace accommodations, change in perceived efficacy in patient-physician interactions (PEPPI), and symptom burden. We will ask participants about accommodations requested at baseline and at each on-treatment and post-treatment survey. Those who report asking for accommodations will also be asked to report on whether their request was granted, including whether the request was granted in full, in part, or if they were given a different accommodation instead. Symptom burden will be assessed using relevant items from the Patient-Reported Outcomes version of the Common Terminology Criteria for Adverse Events (PRO-CTCAE®). Details of these analyses are included below. These four secondary outcomes will be evaluated with respect to their relationship with the primary outcome.

The endpoint for the exploratory aim is treatment adherence based on relative dose intensity (RDI), a measure that incorporates both chemotherapy dose-reductions and treatment delays, and for which a standard exists that can be compared across chemotherapy regimens. RDI is expressed as a percent; the commonly accepted threshold below which adjuvant chemotherapy for breast cancer is less effective is 85% [43–45].

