### Sample size {14}

*Sample size for Aim 1:* Based on the standards for usability testing codified by Jakob Nielsen and recommended by the Department of Health and Human Services [46–48], an iterative design using 3 waves of 3–4 participants each is needed to optimize usability when 2 distinct groups of users are tested (i.e., English and Spanish speakers). Therefore, we anticipate that we will complete usability testing with 18-24 participants. We will do additional usability testing if significant usability issues continue to be identified during the third wave of usability testing.

*Sample size for Aim 2:* The sample size calculations for the proposed study are based on the findings of the BCW study [7], our prospective, longitudinal, observational study of disparities in employment outcomes. The study sample in BCW [7] is similar to that anticipated for the proposed study (based on eligibility criteria and recruitment sites). In BCW [7], 82% of participants completed 4-month follow-up surveys, 79% completed 1-year follow-up surveys, and 58% completed 2-year follow-up surveys. Based on these data, we anticipate that at least 80–85% of participants in the proposed study who complete baseline assessments will also complete the 4-month assessment and, therefore, be evaluable for the primary endpoint. In contrast to the BCW study [7], which was observational only and in which there was no contact with participants between the baseline and 4-month post-treatment survey, the proposed study is testing an intervention and will include several points of contact throughout the treatment period. We anticipate greater participant engagement in the proposed study and, therefore, higher retention than observed in the BCW study [7]. Nevertheless, for the purposes of sample size calculation, we will use the BCW study [7] retention statistics as a conservative estimate. For the 1- and 2-year endpoints, we expect retention to be at least 80% and 60%, respectively.

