After verifying eligibility and completing the informed consent process with those who wish to participate, study staff will give participants instructions on how to log onto the study website to complete an online survey at a later date, directions on how to complete the survey on an iPad in clinic, or administer the survey interview-style. At the time of enrollment, we also will ask participants to provide contact information for themselves as well as for two emergency contacts who we may reach in case we are unable to contact the participant for administration follow-up surveys. We will call each participant who has not completed a baseline survey within 1 week of enrollment to offer the opportunity to complete a survey interview-style (if participant prefers that to an online survey) or to remind the participant to log onto the website. If the participant prefers to complete a survey interview-style, the research staff will administer the survey and enter participant responses directly into the online survey in real time, on the participant’s behalf.

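### The protocol says lack of blinding can only shrink the arm difference; with self-reported outcomes it may also favour the app, and assigning the arm at consent lets staff who know it collect baseline answers

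*Protocol article*

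**What the plan says.** Section {17a} accepts that "it is not possible to blind participants or providers to the assigned treatment". It then states the direction of any resulting bias: "Any tainting of our findings due to non-blinding would be anticipated to diminish our finding of a difference between treatment arms", and adds "rather than supporting a finding of a difference where there is none". No reason is given for either half.

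Under Outcomes {12}, "The primary endpoint of the trial is self-reported employment status 4 months following the completion of treatment". The section on RCT surveys and measures makes everything else self-reported too, apart from cancer-related clinical variables and chemotherapy adherence.

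On procedure, section {16c} says that once consent is given "the consenting professional will sequentially assign the participant to the intervention or the control arm identified in the randomization list". The consent section {26a} describes that person as a research team member, generally a clinical research coordinator. The only safeguard in section {16b} is that participants are asked to "complete their baseline survey prior to being informed of their study arm assignment". The baseline survey may be done after enrolment, with a call to anyone who has not completed it within a week. If the participant prefers an interview, "the research staff will administer the survey and enter participant responses directly into the online survey in real time". The section on RCT surveys and measures also allows staff to administer baseline and on-treatment surveys by telephone or in person. Where a follow-up survey is not returned, it provides for contact, including by telephone, to verify employment status.

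**The concern.** In an open trial with self-reported outcomes, bias has no fixed direction. Controls who seek outside help dilute the effect. App users who give the answers the app encourages, or who report more favourably because they received the newer format, inflate it. The app is built to raise self-efficacy, and self-efficacy is among the things participants then report. A sentence that admits only dilution would let a positive secondary result be presented as safe from inflation.

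The stated procedures add a second, smaller route. Section {16b} is headed as the concealment mechanism, but it describes withholding the arm from the participant, not from the staff member who assigned it. If assignment comes straight after consent and an interview-style baseline follows, the interviewer may already know the arm. Outcomes {12} lists change in PEPPI as a secondary endpoint, so baseline PEPPI is part of an outcome and not merely descriptive.

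**Working it through.** **The plan's own figures.** Inputs from Sample size {14}: 167 per arm, two-sided 5%, PEPPI mean 38 and SD 12, target 42; primary endpoint 50% against 65% with 80% power.

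- PEPPI: SE = 12 × √(2/167) = 1.313. For a 4-point difference, 4/1.313 = 3.046, and power = Φ(3.046 − 1.960) = 86.1%. This agrees with the plan's figure of more than 85%.
- Primary: n = (1.960 + 0.842)² × (0.50×0.50 + 0.65×0.35)/0.15² = 166.6, so 167 per arm, as stated.

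The planned sample size is not in dispute.

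**If there is no true effect but app participants report higher PEPPI.** The documents give no size for reporting bias, so the shifts *b* are assumptions. The two-sided false-positive rate is 1 − Φ(1.960 − b/1.313) + Φ(−1.960 − b/1.313).

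| Assumed PEPPI shift | b/SE | False-positive rate |
|---|---|---|
| 0 | 0 | 5.0% |
| 0.5 point | 0.381 | 6.7% |
| 1 point | 0.762 | 11.9% |
| 2 points | 1.523 | 33.1% |

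Two points is half the difference that the plan aims to detect.

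**The same check on proportions.** With n = 167 per arm, d = p₂ − p₁ and p̄ the mean of the two reported rates, the cut-off is c = 1.960 × √(2p̄(1 − p̄)/n). The chance of a false finding for the app is 1 − Φ((c − d)/se), where se = √[(p₁(1 − p₁) + p₂(1 − p₂))/n]. With no shift it is 2.5%.

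- Employment, 50% in truth in both arms: 7.9% with an assumed 3-point shift in the app arm. With 5 points, c = 0.1071 and se = 0.0546, so 1 − Φ((0.1071 − 0.05)/0.0546) = 14.8%.
- Improved confidence, 30% in both arms: 16.2% with an assumed 5-point shift.

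**The opposite direction.** If the true rates are 50% and 65% but controls are reported 5 points too high, power falls from 79% to 46% by the same pooled-variance formula. Dilution is real too, so the error in section {17a} is that it recognises only that direction.

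**Order of events.** Section {16c} places assignment once consent is given. The RCT recruitment section allows the baseline survey to come later and to be staff-administered. Section {16b} shields only the participant. Nothing in the article separates the person who assigns from the person who interviews, and nothing says that they are the same.

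**The case against.** Several counter-arguments have weight.

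- **The primary endpoint is little exposed.** Working or not working is fairly factual. The post-treatment surveys start with an email, and staff contact there is mainly reminders and verification after non-response. A reader might infer that the primary result is compromised; the documents do not support that.
- **The comparator is active.** The booklet carries most of the app's content, which plausibly narrows the gap in expectation. This reduces the likely size of the bias but does not fix its direction.
- **Part of baseline is protected.** Confidence in asking an employer is measured at eligibility, before assignment, and employment is an entry criterion. What remains exposed is the rest of the baseline survey, notably PEPPI and symptoms.
- **The article condenses a fuller protocol.** A reader might infer that one person both assigns and interviews, or that recruiters can foresee the next assignment. Neither is stated. The list is generated by the biostatistics department and held in REDCap. The article also does not say outright that the arm is drawn before the baseline survey; that is the more natural reading of section {16c}. Missing detail on staff roles is not itself an error. The direction-of-bias sentence is different, because it is a stated claim.
- **The shifts are assumed.** A half-point PEPPI shift yields only 6.7%. The calculation shows that inflation is possible, not how large it will be.

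A reader might also infer that enrolment is too small, because the retention assumption is framed around women "who complete baseline assessments will also complete the 4-month assessment" while 420 counts everyone recruited. This is immaterial. Even if 97% completed baseline (an assumption), the 82% retention seen in the earlier observational study gives 420 × 0.97 × 0.82 = 334, the number required.

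**Conclusion.** The direction-of-bias statement in section {17a} is wrong as written and should be replaced. Bias may run either way, and it may favour the app chiefly on confidence in asking an employer, PEPPI, accommodations and PRO-CTCAE symptoms. Chemotherapy adherence comes from records and is outside the argument.

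The PEPPI false-positive rates of about 12% and 33% rest on assumed shifts of 1 and 2 points with the plan's SD of 12 and 167 per arm. They are illustrations, not estimates. The procedural part holds as a possibility: as the steps are written, staff who know the arm may collect baseline PEPPI and symptoms. The planned sample size stands, and no planned analysis depends on the sentence. What is at stake is how positive self-reported results would be interpreted, together with an avoidable exposure at baseline.

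**What to change.** 1. Replace the sentence in section {17a} with a statement that bias from non-blinding may run in either direction and may favour the app on self-reported secondary outcomes. Cost: wording.
2. Release the REDCap assignment only after eligibility, consent and a submitted baseline survey. Participants are already meant to finish that survey before learning their arm, so this delays nothing for them. Cost: a REDCap setting.
3. Record how each survey was completed (self-administered or by interview) and report a sensitivity analysis by mode. Cost: one field and one additional analysis.
4. Where existing staffing allows, hide the arm field from staff who conduct interview-style surveys and employment-verification calls, using the user and group privileges that REDCap already has. Cost: rota planning, which is harder where bilingual staff are needed. The masking will be partial. Participants can reveal their arm, and staff who call women reporting unfair treatment have to ask whether the app or the booklet was the cause.

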### Procedure for unblinding if needed {17b}

Participants will not be blinded regarding their assigned intervention arm.

## Data collection and management

### Plans for assessment and collection of outcomes {18a}

#### Usability testing

Clinical research coordinators (CRCs) will record the participant’s verbal and non-verbal expressions while performing several tasks using the TEAMWork App. Participants will be permitted to use the TEAMWork Help Section as a guide when having difficulty completing a task. Participants will be asked to complete an Early User Experience Survey after the usability test. The survey, which will take approximately 10–15 min to complete, asks about their experiences using the app, including which features they like or dislike and if any aspects of the app’s content or functionality are unclear or difficult to use. Participants will also be asked if there is anything they would change, remove, or add. This survey also includes questions about participant demographics and their cancer history. This survey will be self-administered electronically on a study iPad. Participants not able to complete this survey in clinic will be given a link they can use to take the survey from home within 1 week of their consent date. In total, the usability testing procedures and Early User Experience Survey will take approximately 30–60 min to complete. Due to time constraints in clinic and the ongoing adjustment of the TEAMWork app during this phase, not all tasks and questions will be completed by each usability testing participant.

#### Focus groups/interviews

##### Focus groups

Introductions and a set of guidelines will be presented to participants at the beginning of the focus groups. Once all participants have acknowledged this set of rules, the facilitator will begin with questions from each section. A focus-group guide will be used as a blueprint for key discussion topics. Due to time constraints, it is possible that not all questions will be addressed. The moderator will guide the groups’ conversation to stay on time while providing information on all the topics, as listed below.Content of the mobile app (20 min)Content of the videos (50 min)

Each focus group will last approximately 1.5 h, including the introduction and guidelines (10 min), topics (70 min), and wrap-up (10 min).

Audio recordings of focus group discussions will be transcribed (and translated, if appropriate) for subsequent qualitative analysis.

##### Interviews

Interviews will use the same guide as the focus groups as a blueprint for key discussion topics. Due to time constraints, it is possible that not all questions will be addressed. The interviewer will ask the participant their thoughts on the content of the mobile app and content of the videos. Each interview will last approximately 1 h and 30 min. Audio recordings of the interviews will be transcribed (and translated, if appropriate) for subsequent qualitative analysis.

#### RCT surveys and measures

Baseline and on-treatment surveys will be administered by study staff over the telephone or in person (staff will enter participant-reported data into the study electronic database in real time), self-administered by patients in clinic using dedicated study iPads, or self-administered at home, based on participant preference. A summary of the timing of surveys for the RCT is included in Table 1, and the surveys are further described in detail below. Participants will be encouraged to complete the surveys in the clinic, but those unable to do so will be provided with a link they can use to access a survey from home every attempt will be made to administer the survey on the day on which the treatment had originally been scheduled, as symptom-related questions in the on-treatment surveys refer to the time since the preceding chemotherapy cycle. However, if this is not possible, then the survey will be administered as soon as it is practicable to do so. Participants will be contacted by email 4 months, and 1 and 2 years after treatment completion for follow-up surveys to assess employment status and related outcomes. We will call and/or send email reminders to participants asking them to take each survey, and if we do not receive a response, we will call, email, and/or send a postcard to participants to verify employment status.

All variables will be self-reported, except for cancer-related clinical variables and chemotherapy adherence. Prior research has shown limited accuracy in medically underserved breast cancer patients’ self-reporting of type of breast and axillary surgery [51]. Therefore, the research staff will review the medical records to capture clinical information about the breast cancer diagnosis and its treatment.

#### Baseline survey

Participants will complete a baseline survey that captures detailed information about demographic characteristics, place of birth, acculturation based on language (if appropriate), family structure, comorbid conditions, occupation/industry, work environment and job tenure, job tasks, union membership, and income (household and individual), which will be analyzed as a function of the federal poverty level to account for household size and secular trends [8, 52, 53]. Financial worry and distress will be assessed using the 12-item Comprehensive Score for financial Toxicity (COST). The baseline assessment will also include an assessment of symptoms using the National Cancer Institute PRO-CTCAE® and of perceived efficacy in patient-physician interactions (5-item PEPPI) [54, 55]. These measures will be combined with the measure of self-efficacy to ask an employer for accommodations (which was assessed at the time of eligibility determination). All measures used are from existing instruments that have been validated (either externally or by members of the research team) and translated into Spanish using standard methods [56].

#### On-treatment surveys

To limit participant burden, on-treatment surveys will be completed at approximately the mid-point of chemotherapy and with the last cycle only. Although the time between surveys will vary based on the regimen prescribed, the number of surveys administered to each participant will not vary. Participants whose chemotherapy regimen changes after treatment initiation will be surveyed at the projected mid-point of the regimen (on average 5–10 weeks). Such a change in adjuvant treatment regimen is rare and is not expected to affect study results. Moreover, detailed treatment information will be captured, and any effect of such a change will be evaluated in sensitivity analyses. These surveys will include an assessment of symptoms, accommodations, work status, and the two measures of self-efficacy (to ask an employer for accommodations and in patient-physician interactions).

Symptom control will be assessed using the NCI’s PRO-CTCAE®, which has been validated in English and Spanish [57, 58]. The scale may be used to measure symptoms over a period of anywhere between 1 day and 4 weeks [59]. Standard chemotherapy regimens for breast cancer have cycles varying in length from 1 to 3 weeks. Therefore, we will ask each patient to recall symptoms over the duration of the period since the last cycle of treatment. For example, if a patient is receiving chemotherapy on a 2-week cycle, her surveys will refer to her experience of symptoms over the course of the preceding 2 weeks. However, if she is receiving treatment on a 3-week cycle the questions will refer to the preceding 3 weeks.

Receipt of workplace accommodations will be assessed by asking participants about the kinds of accommodations they have requested, and whether these have been granted, including if the request was granted in full, in part, not at all, or if something else was offered in its place. Work will be measured in terms of employment status, work hours, and participant choice regarding these outcomes. Additional assessments will include self-efficacy to ask for accommodations and in patient-physician interactions.

Self-efficacy to ask for accommodations will be measured using a 5-item tool that we have developed and validated for this purpose (manuscript in preparation).

As patients in both study arms may access informational resources external to the study but which could affect the outcome, we will ask about resources they may have accessed (e.g., websites, support groups, etc.).

Financial worry and distress will be assessed using the 12-item Comprehensive Score for financial Toxicity (COST).

